### Secondary clinical outcomes

Clinical outcome data collected through the chart audit will be used to determine the change in the proportion of patients who were at target levels (as specified in the Champlain CVD Prevention and Management Guideline) for each clinical indicator upon completion of the intervention.

### Sample-size calculation

Prior to the recruitment phase of this project, a series of simulations were run on patient data from a pilot phase of the chart audit in order to examine how the primary outcome composite score varied with specific changes in physician adherence to recommended guidelines. For example, if Patient X had diabetes and a composite score of Y, how would Patient X's composite score change if he/she now had (a) a discussion about glycemic control medications with his/her physician? (b) a lipid profile test performed? (c) both maneuvers performed? The results from each simulation were discussed amongst a panel of family physicians and cardiologists in order to assess what effect size or change in composite score would represent a clinically relevant change in provider performance. From these discussions, it was agreed that an effect size (mean difference in the composite score for practices in the intervention step vs. the comparison step) of 8% represented a clinically relevant change. Using the sample-size calculation formulas for comparing two means presented by Donner and Klar [45], and assuming an intra-cluster correlation coefficient (ICC) of 0.18, a common standard deviation of 18%, and an average of 66 charts per practice, we would require 21 practices per step to detect an 8% difference using a two-sided test at the 5% level of significance with 90% power. To account for 20% potential attrition, a total of 27 practices per step were enrolled. The ICC and standard deviation used for this calculation were derived from the IDOCC pilot project on nearly 500 patients across seven practices. The anticipated attrition rate accounted for both practice-level as well as patient-level attrition and was based on experience from previous practice-based research studies [27-29].

### Data analysis

A mixed-methods approach will be used, which will consist of analysis of both quantitative data and qualitative data.

### Quantitative analysis

Descriptive statistics will be generated for all project variables (means and standard deviations for continuous variables with normal distributions or medians and interquartile ranges for skewed distributions, and frequencies and proportions for categorical variables). These statistics will be compared among the practices allocated to the different steps of the stepped-wedge design to assess imbalances in practice characteristics that would need to be controlled for in the analyses, including age, sex, practice model type, urban/rural practice setting, practice size, patient socioeconomic status (determined using a census-based method [46]), and patient comorbidities. Physicians agreeing to participate in the project will be compared to those declining to participate, and those characteristics significantly associated with participation will be adjusted for in secondary analyses to explore the potential impact of participation bias on our results. All analyses will be conducted using a commercially available software package (SAS, Version 9.2, SAS Institute, Inc., Cary, NC, USA [47]) with α = 0.05 as the level of significance.

Although the practice is the unit of intervention, all process and clinical measurements are at the patient level, and as such, the patient is the unit of analysis. All primary and secondary outcomes will be analyzed using general linear mixed-effects regression models using the stepped-wedge design analysis approach outlined by Hussey and Hughes [48]. All models include random effects for practice to account for the ICC of patients within the same practice, as well as fixed effects for region (the stratification used in the randomization scheme).

Prespecified controlled comparisons (Table 1) among practices in specific steps will be made in the regression models to examine the impact of the intervention while controlling for the effects of time. For example, in order to estimate the impact of the intensive phase of the project on Step I practices, a comparison of the patients in the intervention (Step I) and control (Step II) groups will be done by comparing the mean changes in the primary (*i.e*., QOC composite score) and secondary outcomes from baseline (Time Period 1) to the intensive phase year (Time Period 2) (Table 1).

In addition, since we are serving such a diverse group of patients with varying comorbidities, the number of indicators for which each patient is eligible varies; thus, certain patients may have a greater impact on statistical estimates of the primary outcome composite score than others. For example, if Patient A was eligible for 4 maneuvers and Patient B was eligible for 8, a change in one maneuver for Patient A results in a 0.25 change in the composite score, while the same change for Patient B only results in a change of 0.13. A "performance indicator eligibility" covariate will be included in the regression model in order to account for the differences in the number of performance indicators for which each patient was eligible.

A backwards stepwise approach will be used to establish regression models in which only variables significant at the α < 0.1 level remain.

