### Data collection

The primary source of data collection consists of repeated chart audits [42] of the same randomly selected patient population from each participating practice. Chart Abstractors visit practices on two separate occasions to collect chart data--once pre-intervention and once postintervention.

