### Post-intervention

After Year 2 of the intervention has ended in each practice, Chart Abstractors will return to collect medical chart data from both intervention years (*i.e*., Year 1: intensive phase, Year 2: sustainability phase) and to also collect pre-intervention baseline control data (Figure 2: Baseline-C). Participation in the follow-up data collection is encouraged through the following practices: (a) practices sign a consent form stating that they will allow a post-study follow-up, and (b) each practice is told that they will receive an end-of-study progress report highlighting changes in patient health and adherence to evidence-based guidelines.

Other data sources include Facilitator narrative reports, which are essentially field notes recorded after each practice encounter, including visits, email, and telephone encounters.

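### With only a practice random effect named, a model fitted to period-level scores misstates the standard error of the change contrasts, in a direction the article does not determine

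*Protocol article*

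**What the plan says.** **Data.** Under Data collection, the main data source is "repeated chart audits [42] of the same randomly selected patient population from each participating practice". Under Post-intervention, "Chart Abstractors will return to collect medical chart data from both intervention years", and a baseline control period is abstracted at the same visit. Under Sample-size calculation, "The anticipated attrition rate accounted for both practice-level as well as patient-level attrition", which fits a cohort of patients who are followed. Each patient therefore contributes several scores.

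**Contrasts.** Table 1 defines every comparison as a change between two time periods. All but the Step II sustainability comparison are set against another step's change over the same periods. Under Quantitative analysis, the example for Step I is made by "comparing the mean changes in the primary" and secondary outcomes between Time Periods 1 and 2.

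**Model.** In the same section "the patient is the unit of analysis", and outcomes are analysed with "general linear mixed-effects regression models using the stepped-wedge design analysis approach outlined by Hussey and Hughes". On dependence it says: "All models include random effects for practice to account for the ICC of patients within the same practice". Region enters as a fixed effect. The article names no patient effect, within-patient covariance, practice-by-period effect or robust standard error.

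**The concern.** A practice effect that stays constant over time cancels from a change. The precision of a change then depends on two other quantities: how strongly a patient's scores correlate between periods, and how far a practice's own level drifts between periods. The reason given for the random effect concerns different patients in the same practice and covers neither.

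The two omissions are distinct and act in opposite directions.

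- **No patient effect.** This follows from auditing the same patients. The model treats a patient's repeated scores as independent given the practice, so the reported SE of a change is too large and the test conservative.
- **No practice-by-period effect.** This has nothing to do with re-auditing the same patients and would arise with fresh samples too. The model treats practice drift as if it averaged out over the 66 charts, so the reported SE is too small and the test anti-conservative.

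At stake are the confidence intervals and the 5% level for the primary outcome contrasts. The article gives some reason to expect drift: practices choose their own goals, and delivery system redesign is tailored to each practice's needs and resources.

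**Working it through.** **1. The plan's own figure.** From Sample-size calculation: difference 8, SD 18, ICC 0.18, 66 charts, two-sided 5%, 90% power.

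- Patients per group without clustering: 2 × [18 × (1.960 + 1.282)/8]² = 106.4.
- Design effect: 1 + 65 × 0.18 = 12.7.
- Practices per step: 106.4 × 12.7/66 = 20.47, so 21. With 20% attrition, 21/0.8 = 26.25, so 27.

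Both stated figures reproduce. The calculation compares two means at one time point and uses neither correlation at issue here.

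**2. Inputs for the change contrast.** Step I has 26 practices and Step II has 30 (Table 2). The total variance is 18² = 324.

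- Practice variance: 0.18 × 324 = 58.32.
- Within-practice variance: 0.82 × 324 = 265.68.
- 1/26 + 1/30 = 0.0718.

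Two quantities are **assumed**, because the article does not give them:

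- r, the correlation between periods of a patient's deviation from the practice level (0.3 to 0.7);
- CAC, the cluster autocorrelation, meaning the correlation between periods of a practice's own level (0.80 to 1.0).

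Practices are taken as independent, as in the plan's own calculation.

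**3. SE reported by the practice-only model on period-level scores.**

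Variance ≈ 2 × [265.68 + 58.32 × (1 − CAC)/2]/66 × 0.0718.

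At CAC = 1 this is 2 × 265.68/66 × 0.0718 = 0.578, so SE = 0.76. At CAC = 0.80 it is 0.77. The value does not depend on r.

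**4. True SE of the difference in changes.**

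Variance = 2 × [58.32 × (1 − CAC) + 265.68 × (1 − r)/66] × 0.0718.

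At r = 0.5 the patient part is 2 × 265.68 × 0.5/66 = 4.025:

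- CAC 1.0: (0 + 4.025) × 0.0718 = 0.289, SE 0.54
- CAC 0.95: (5.832 + 4.025) × 0.0718 = 0.708, SE 0.84
- CAC 0.90: (11.664 + 4.025) × 0.0718 = 1.126, SE 1.06
- CAC 0.80: (23.328 + 4.025) × 0.0718 = 1.964, SE 1.40

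**5. Type I error** = 2 × [1 − Φ(1.96 × reported SE/true SE)]. Each cell gives the true SE, then the type I error.

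| CAC | r = 0.3 | r = 0.5 | r = 0.7 |
|---|---|---|---|
| 1.0 | 0.64; 1.9% | 0.54; 0.6% | 0.42; below 0.1% |
| 0.95 | 0.91; 10.0% | 0.84; 7.6% | 0.77; 5.2% |
| 0.90 | 1.11; 17.9% | 1.06; 15.8% | 1.01; 13.6% |
| 0.80 | 1.44; 29.6% | 1.40; 28.2% | 1.36; 26.8% |

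A simulation under no effect (2,000 runs per setting, r = 0.5) gave a mean model SE of 0.76 to 0.77. Rejection rates were 0.5%, 7.7%, 15.8% and 26.9% at CAC 1.0, 0.95, 0.90 and 0.80.

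**6. Where the two errors cancel.** Setting the true variance equal to the reported one, and ignoring the small drift term in the latter, gives 1 − CAC ≈ (0.82/0.18) × r/66 = 0.069 × r. The break-even CAC is 0.979, 0.965 and 0.952 for r = 0.3, 0.5 and 0.7.

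**The case against.** **The article does not say that practice is the only random effect.** It says that models include it, and the sentence is plainly not a full specification, since it does not list time or treatment either. A fuller plan could add terms. This stands as a limit on certainty. It does not dispose of the point: time and treatment are implied elsewhere in the same section, whereas nothing in the article implies a patient or practice-by-period term. The stated reason for the random effect is confined to correlation between patients of one practice.

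**A change-score reading largely removes the defect.** The section speaks of comparing mean changes, and Table 1 has a column for change in outcome. If the response is each patient's change, the patient effect drops out and a random practice effect on changes captures practice drift. A simulation of that analysis (4,000 runs, r = 0.5, 54 degrees of freedom) gave type I error of 4.1%, 4.9%, 4.6% and 5.5% at CAC 1, 0.95, 0.90 and 0.80. The text permits this reading but does not state it. It equally permits a model on period-level scores, so the ambiguity needs to be closed.

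**The practical effect is bounded.** The relevant difference is 8 points, and even the largest SE at r = 0.5 leaves 8/1.40 = 5.7 SEs. With a reported SE of 0.76, significance starts near 1.96 × 0.76 = 1.5 points, so most false positives would lie well below 8. That is fair for a large effect. It does not help a small observed effect or the width of the confidence intervals.

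**Conclusion.** The point holds conditionally. Fitted to period-level scores with the practice effect as the only random effect, the model reports an SE of about 0.76 for Step I against Step II almost whatever the truth. At an assumed patient correlation of 0.5, the true SE runs from 0.54 (CAC 1.0) to 1.40 (CAC 0.80), and type I error from about 0.6% to 28%. The 5% level is met only where the two errors happen to cancel, at CAC of about 0.95 to 0.98 for patient correlation from 0.7 down to 0.3.

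A reader might infer three stronger things that the article does not support.

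- *That the 5% level certainly fails, or fails on the liberal side.* Neither correlation is given, cancellation is possible, and the change-score reading would largely remove the problem.
- *That auditing the same patients causes the inflation.* On its own it makes the test conservative; inflation comes only from the missing practice-by-period term.
- *That the sample size is wrong.* The 21, then 27, practices per step reproduce and are not in question.

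The result also rests on reading the repeatedly audited patient population as the same individuals, which the allowance for patient-level attrition supports.

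**What to change.** Under Quantitative analysis, state one of the following:

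- the models for period-level scores include a random effect for patient within practice and a random practice-by-period effect, as well as the practice effect; or
- each Table 1 contrast is fitted to within-patient change scores with a random practice effect.

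For these two-period contrasts the two options serve the same purpose, and either lets the data determine both correlations.

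The cost is wording and programming, with no new data, provided records can be linked by patient across audits. The article does not state that they can, although repeat audits of the same patients imply it. Table 2 shows Step II final data collection starting in October 2011, after its April 2011 status date. The wording could therefore be settled before the control data for the Step I intensive-phase contrast are complete.

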### Study setting

The project is set in primary care practices in the Champlain Local Health Integration Network (LHIN) located in Eastern Ontario, Canada. The Champlain LHIN is a culturally diverse region with a population of 1.2 million people who have chronic disease burdens and patient health outcomes that are comparable to Ontario and the rest of Canada [33]. Excluding walk-in clinics, all models of primary care practices in the selected geographic areas of the Champlain LHIN are eligible to participate in this project, including solo practices, group practices, community health centers, and academic health center teaching practices.

The Champlain LHIN was first divided into nine geographic regions using Geographic Information System mapping technology [34] and then the regions were grouped together into strata by their location (*i.e*., west, central, and east) (Figure 3). Next, a computer-generated randomization assigned each region within each stratum into one of the three steps. Randomization at the regional level was done (a) to ensure that each step was comprised of one region from each stratum (east, central, and west), (b) to ensure that each region per stratum had the same probability of being in any given step and thus the same probability of beginning the intervention at any given time point, and (c) because practice-level randomization was logistically impractical for traveling between practices randomly scattered throughout this large health region (16,000 sq. km). Using provincial administrative data, practice-level (*i.e*., practice model type, rurality, average physician age, gender mix) and patient-level (*i.e*., age, sex, socioeconomic status, number of comorbidities) characteristics of practices that consented to take part in IDOCC will be compared across the nine regions and across the three steps to assess any nonandomness of the randomization process, as well as across all practices and patients in Ontario to assess provincial representativeness.

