Another limitation of this study is that the timing of the intervention was randomly assigned at the regional level. A more powerful approach would have been to have random assignment at the practice level. Although ideal, practice-level randomization was logistically impractical for a project of this size, as traveling between different practices that are randomly scattered throughout this large health region (16,000 sq. km) would have greatly increased project costs and extended project timelines. By having practices grouped into regions, Outreach Facilitators and Chart Abstractors were able to visit multiple practices within a given day, something that would be difficult in a practice-randomized study.

Finally, we acknowledge the limitations of using medical chart data. Studies have demonstrated that direct observation can often identify more details about care delivery than chart audits; however, none of these studies have quantified how big this gap is [62,63]. As such, it is likely that we will underestimate the number of procedures carried out. However, numerous studies have demonstrated that chart review is the gold standard for collecting medical data as direct observation is prohibitively expensive and not feasible for a trial this large and administrative data are generally less reliable than chart data [63]. This discrepancy will affect our generalizability when we talk about the regional adherence to the Guidelines, but it should not affect the evaluation of our intervention as the same limitation applies to the data collected in all steps and all time periods.

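### The analysis model calls the nine randomised regions the stratification and has random effects for practice only, so region-specific change over time can make confidence intervals too narrow

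*Protocol article*

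**What the plan says.** Study setting in the protocol article describes the allocation. "The Champlain LHIN was first divided into nine geographic regions"; "then the regions were grouped together into strata by their location" (west, central, east); and "a computer-generated randomization assigned each region within each stratum into one of the three steps". One aim was "to ensure that each step was comprised of one region from each stratum (east, central, and west". Limitations repeats that "the timing of the intervention was randomly assigned at the regional level". The randomised units are therefore nine regions, three per step, and the stratification factor is location, with three levels.

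Quantitative analysis specifies linear mixed models on the Hussey–Hughes stepped-wedge approach. On clustering it says: "All models include random effects for practice to account for the ICC of patients within the same practice". The only term for region is then given in these words: "as well as fixed effects for region (the stratification used in the randomization scheme". It gives no random effect above practice and no term for change over time within a region. Table 1 defines each controlled comparison as a difference between steps in change from one period to another.

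**The concern.** The two sections disagree about what region is. A programmer cannot tell whether to code three location strata or nine regions.

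The larger issue is that the random effects stop at practice, one level below the unit that was randomised. Practices in one region share local services, and the article's own Guideline lists community resources region by region. If care in a region drifts for local reasons, all its practices drift together. That shared drift enters a Table 1 contrast directly, while the model treats it as independent variation between practices. Intervals for the composite score would then be too narrow, and a nominal 5% test would reject too often. Limitations mentions regional assignment only as a loss of power, not as something the analysis must reflect.

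**Working it through.** **1. The plan's own figure.** Inputs from Sample-size calculation: difference 8, SD 18, ICC 0.18, 66 charts per practice, two-sided 5%, 90% power.

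- Design effect = 1 + 65 × 0.18 = 12.7.
- Practices per step = 2 × [18 × (1.960 + 1.282)/8]² × 12.7/66 = 20.47, rounded up to 21.
- With 20% attrition: 21/0.8 = 26.25, so 27.

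Both figures reproduce, with practice as the only level of clustering. Table 2 gives 26 + 30 + 27 = 83 practices, in nine randomised regions.

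**2. Constant region differences.** I compared the model standard error with the true one for a Hussey–Hughes model with 83 practices, four periods and a practice intercept. With an assumed time-constant region ICC of 0.05, the ratio of true to model SE is 1.00 with nine region indicators and 1.01 with three stratum indicators. Constant differences are not the problem under either coding.

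**3. Region-specific change, with practice-level change variance estimated from the data.** The documents do not give the cluster autocorrelation (assumed 0.8), the correlation of a patient's repeated scores (assumed 0.5) or the region-by-period SD s (assumed 1, 2 or 3 points).

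- Between-practice variance: 0.18 × 324 = 58.32. Practice-by-period part: 0.2 × 58.32 = 11.66.
- Within-practice variance: 0.82 × 324 = 265.68.
- Variance of one practice's change: 2 × 11.66 + 2 × 265.68 × 0.5/66 = 23.33 + 4.03 = 27.35.
- Two-step contrast without region-by-period variation: 2 × 27.35/27 = 2.026, SE 1.42.
- True variance: 2.026 + 2 × (2s²/3) = 2.026 + (4/3)s².
- Variance the analysis expects: (2/27) × [27.35 + 2s² × 18/26]. With nine practices in each of three regions, the practice-level variance within a step picks up (27 − 9)/26 of the region part, but divides it by 27 practices rather than 3 regions.
- Type I error = 2 × [1 − Φ(1.96/SE ratio)].

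| s (points) | True variance | Model variance | SE ratio | Type I, formula | Type I, simulated |
|---|---|---|---|---|---|
| 1 | 3.36 | 2.13 | 1.26 | 11.9% | 11.7% |
| 2 | 7.36 | 2.44 | 1.74 | 25.9% | 25.6% |
| 3 | 14.03 | 2.95 | 2.18 | 36.9% | 36.6% |

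With stratum effects in the model, the simulated values are about 12%, 27% and 40%. A t-test on the six region mean changes with 4 degrees of freedom held 5% at each s.

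**4. Practice intercept only.** This check ignores patient correlation and practice-by-period variation. The two-period contrast has model SE √[4 × 265.68/(66 × 27)] = 0.77. With s = 1 the true SE is √(0.596 + 1.333) = 1.39, and type I error is about 28%. In the four-period model of step 2, an assumed region-by-period ICC of 0.0025, 0.005 or 0.01 (SD 0.9, 1.27 or 1.8 points) gives SE ratios of about 1.7, 2.2 and 2.9, and type I error of about 25%, 36% and 50% under either coding.

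**5. Randomised units.** A two-step contrast has six regions. Treated as independent units they leave 4 degrees of freedom, with critical t 2.78 instead of 1.96. The whole design has (3!)³ = 216 stratified allocations.

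**The case against.** The strongest reply is that the planned contrasts are changes within practices, so practice intercepts and region fixed effects already remove what regions have in common. For constant differences this is right, as step 2 shows. A reader might infer from the practice-only random effects that region clustering is ignored altogether, or might compute inflation from a cross-sectional comparison of step means. The documents support neither. Under both codings constant differences largely cancel, and a cross-sectional comparison is not the analysis specified.

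A second reply is that every variance behind the inflation is assumed. That also stands. At s = 3, region would hold 9/(9 + 11.66) = 44% of the period-to-period cluster variance, which nothing in the documents supports. If regional trends are nil, the variance inflation disappears.

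Third, a reader might infer that all practices in a region cross over together. Practice recruitment says practices entered on consenting, so starts within a step were staggered. Facilitators are also a weak example of a shared influence: no section assigns them by region, and an effect of facilitation is absent under the null hypothesis.

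Finally, regional allocation is disclosed and justified, and a degrees-of-freedom method is often left to a statistical analysis plan. But the random-effects structure and the stratification label are stated in the article. Neither coding of region covers region-specific change, so disclosure does not repair the standard errors.

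**Conclusion.** The point holds in a limited form. Quantitative analysis contradicts Study setting on what the stratification factor is, and the stated model has no component for region-specific change over time, although regions were randomised and Table 1 contrasts such change. If that change exists, confidence intervals are too narrow. With region-by-period SDs of 1, 2 and 3 points, type I error is about 12%, 25–26% and 37% when practice-level change variance is estimated, and higher with a practice intercept alone. These figures rest on the article's SD, ICC, charts and practices per step, equal regions of nine practices, and the three assumed quantities in step 3. The direction is firm once region-by-period variance exceeds zero; the size is not known from the documents. Even with no such variance, each two-step contrast still rests on three regions against three.

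**What to change.** In Quantitative analysis, replace the sentence on random and fixed effects so that it:

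- names location (west, central, east) as the stratification factor, fitted as a fixed effect;
- says that region means the nine randomised areas, kept as fixed or random;
- adds a region-by-period random effect alongside the practice effects;
- uses small-sample degrees of freedom (Kenward–Roger or Satterthwaite);
- checks the primary p-value with a permutation test over the 216 stratified allocations of regions to steps, using a statistic that draws on all three steps. Swapping only two steps gives 2³ = 8 allocations and a smallest two-sided p of 2/8 = 0.25.

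The cost is analysis wording and a few lines of code; design and data collection do not change. Intervals will be wider. Under the assumptions of step 3 without regional drift, the half-width of a two-step contrast goes from 1.96 × 1.42 = 2.8 points to 2.78 × 1.42 = 3.9 points with 4 degrees of freedom. The region-by-period variance will be estimated from only nine regions and will be imprecise, which is why the permutation check is useful.
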